### Intervention

Figure 1 shows the study flow diagram including time and activities for both groups (see Additional file 1).

The Intervention Arm includes the following:Interdisciplinary intervention led by a clinical pharmacologist who is a leader in evidence-based prescribing—includes a detailed discharge medication reconciliation and management plan focussed on oral anticoagulants at hospital discharge; a circle of care handover and coordination with patient, hospital team, and community providers; three scheduled early post-discharge virtual medication check-up visits at 24 h, 1 week, and 1 month with triage of any problems. Medication reconciliation reviews hospital-administered medications compared to pre-admission medications [35]. Medication management is the more complex task of assessing and revising medications in light of the individual patient’s diagnoses, current symptoms and signs, risk factors, allergies and intolerances, other medications, and goals. In this study, all medications will be reviewed with a focus on OAC choice, dosage, indication, duration, potential drug interactions, patient risk factors for thromboembolism versus bleeding, drug insurance, adherence challenges, and health literacy. A study pharmacist with additional training will complete the detailed medication reconciliation then confer with the clinical pharmacologist who will lead the medication management including meeting with the patient and making prescription changes.Hand-overs to the community care team including the main patient caregiver (if applicable), family physician, medical specialist(s), and community pharmacist, using a templated consult summary note which includes a patient profile, details of recent hospitalization, discharge medications, an OAC monitoring checklist, circle of care and upcoming appointments, and recommendations. Figure 2 shows an example consult note (see Additional file 2)*.* The monitoring is based on (a) best evidence (updated guidelines and dedicated evidence review using the CLOT repository of CanVECTOR and McMaster’s Health Information Research Unit), and decision aid content for patients and their families to assist in anticoagulant knowledge and adherence; (b) best practices regarding discharge medication management, virtual care, scalable coordination of care with clear accountability, communication, and teletriage where situations require medical intervention [5, 16, 19, 36–40]. All consult notes are reviewed in detail with the Clinical Pharmacologist.“Virtual visits” (secure video calls from within our electronic medical record (EMR) or phone visits where video is not possible) by the study pharmacist at three follow-up time points—24 h post-discharge to ensure the discharge prescription medications were obtained and understood, review the OAC monitoring checklist, review other medications, and solicit concerns; and at 1 week and 1 month to ensure medication adherence, review the OAC monitoring checklist and other medications, and solicit concerns. After each follow-up visit, a summary consult note will be sent to all circle of care providers, and any clinical events or serious concerns will be addressed by the Clinical Pharmacologist or directed to patient’s family physician via phone call or direct email. Each follow-up visit with intervention patients will be recorded and tracked to ensure adherence to protocols.Teletriage—The patients have the study pharmacist’s contact information and can phone for assistance at any time. The study pharmacist is in constant communication with a Clinical Pharmacologist investigator for guidance. An expert thrombosis specialist will be available on call as needed.

Control Arm: Patients allocated to the control group will receive usual care, plus the URL to Thrombosis Canada website. Usual care in the participating sites includes OAC management by family doctors except for new thromboembolic events which will be followed short term by thromboembolism or hematology specialists, complicated atrial fibrillation which will have cardiology involved temporarily, and a small proportion of warfarin management which is provided in an anticoagulation clinic. This choice of the control group is the most relevant for generalizability to both academic and community practices.

For both arms, there are no restrictions placed on concomitant medical intervention or treatments, as this is a pragmatic randomized trial.

### Outcomes

Study outcomes, their measurement methods, timing, and analysis are presented in detail in Table 1 and Table 2 and include the following:Primary outcomes, which are study feasibility outcomes, include recruitment and retention rates, and estimated resources required per patient to complete the main trial. Feasibility will be achieved if we can recruit at least 30% of those eligible, retain 90% of those recruited, and spend no more than $1500 per patient running the trial. Secondary feasibility outcomes include barriers and facilitators to success of the primary outcomes, in terms of process and management issues. These will be used to determine whether a large definitive research study is likely to be feasible, taking into account the practical aspects of managing and funding the project [41, 42].Secondary clinical outcomes include the following:The Adverse Anticoagulant Safety Events composite (AASE) which is any of thromboembolic events or clinically relevant bleeding or death. Thromboembolic events include objectively verified ischemic stroke, systemic embolism, pulmonary embolism, or DVT. Clinically relevant bleeds in this study is defined as bleeding that causes death, hospitalization, or emergency department visits.Coordination and Continuity of Care: Adapted from Health Quality Ontario’s draft guidance and a Rand instrument, the Coordination and Continuity of Care Questionnaire is designed to measure the quality of the transitional and follow-up care [5, 43, 44].Patient Quality of Life: The EQ-5D-5L is the 5-level classification system of the EQ-5D, a measure of health status from the EuroQol group [45]. Using EQ-5D-5L, respondents are asked a short series of questions about mobility, self-care, usual activities, pain discomfort, and anxiety/depression, as well as a summary visual analogue scale. This scale, which provides utility measurements, has been well validated for the Canadian population [45–47].Patient Knowledge of OAC Management: Insufficient patient knowledge about OAC may predict poor medication adherence and inadequate anticoagulation control [48]. The COACHeD OAC Knowledge Questionnaire tests knowledge of the therapeutic objective, process of use, safety, and maintenance of the medications [44].Satisfaction with Care: Satisfaction reported by patients and by key health professionals is one of the recommended outcomes to report in medical research, as it may influence adherence [49, 50]. This outcome will be assessed by the Patient/Caregiver Study Satisfaction Survey and by the Provider Study Satisfaction Survey [44].Medication Problems: We will be assessing problems with appropriateness, with medication errors characterized using the National Coordinating Council for Medication Error Reporting and Prevention (NCC-MERP) scale and with medication adherence and attitudes as measured by COMPETE Medication Problems Questionnaire [51, 52].Resource utilization: This is a key outcome to determine cost-effectiveness and cost-utility which then determines whether health care systems might pay for this type of care [53, 54]. We will be measuring all types of health care utilization by patients [43, 46, 54].

**Table 1 Tab1:** Study outcome assessment

Outcomes^**a**^		Variable type	Criteria for success	Outcome measure	Method of analysis
**A. Feasibility outcomes**					
Primary feasibility outcomes	Participant recruitment rates	Continuous (%)	≥ 30% of those eligible will be considered success	Percentage recruited and rate of recruitment (of those screened, of those eligible, and of those approached). Percentage of those recruited (signed informed consent) who complete the end of study assessment at 3 months.	Count of percentages and rates over time
	Participant retention rate	Continuous (%)	≥ 90% is considered success		
	Study resource utilization	Continuous ($CND)	< $1500 per patient recruited and completing the study	Study costs per patient recruited	Cost of personnel, supplies, travel, etc., to run the study/# patients recruited
Secondary feasibility outcomes	Process assessments Management assessments Scientific assessments	Mix of continuous, categorical, and qualitative data	Implementation is successful and feasible, questionnaires are acceptable, and data gathered are reliable and valid	Detailed questions in feasibility assessment	Descriptive
**B. Clinical outcomes**	**Hypothesis**				
Primary clinical outcome	Adverse anticoagulant safety event composite (AASE)	Continuous (%)	Intervention group will have fewer AASE compared to the control group	Count of AASE at the end of the study (3 months). Rates will be expressed as mean rate per patient-year by research assistant.	Chi-square test
Secondary clinical outcomes	Coordination and continuity of care	Continuous	Intervention will have higher ratings than control	Coordination and continuity of care questionnaire partially administered post-discharge and finalized at study end (3 months) by telephone.	*T* tests
	Patient quality of life	Continuous	Intervention will improve more than control	EQ5D-5L—difference in mean change scores at the end of the study.	*T* tests
	OAC management knowledge - patient	Continuous	Intervention will have higher scores than control	OAC knowledge questionnaire	*T* tests
	Satisfaction with care (providers & patients)	Continuous	Intervention will have higher scores than control	Satisfaction questionnaires	Descriptive analysis
	Medication Problems	Continuous	Intervention will have fewer medication problems than control	Composite of OAC-APEQ, COMPETE adherence, and medication error scores	*T* tests
	Cost-effectiveness	Continuous	Intervention will be cost-effective compared to control using a threshold of $50,000 per QALY.	Cost per AASE avoided and cost per quality-adjusted life-years (QALYs)	Economic analysis
	Individual Clinical Events: a) Bleeding events (clinically relevant), b) Thromboembolic events (all); c) Deaths; d) Hospitalizations or ED visits	Continuous	Intervention will have lower event rates than control	Event rate counts from end-study interviews	*T* tests

**Table 2 Tab2:** COACHeD schedule of events

Assessment	Enrolment		Study in-progress			Study end
	Baseline	Hospital discharge	24h	1Week	1 month	3 months
Eligibility screen	A					
COACHeD Brief Assessment of Capacity to Consent	B					
Informed consent	1/C					
Coordination Continuity of Care Questionnaire (CCCQ)	I/C					I/C
EQ-5D-5L v10-Canada	1/C					I/C
OAC knowledge test	I/C					I/C
Randomization and allocation	I/C					
Discharge medication reconciliation and management, circle of care communication and coordination		I				
Virtual Visit Call #1			I			
Virtual Visit Call #2				I		
Virtual Visit Call #3					I	
Adverse anticoagulant safety events (AASE)						I/C
AASE individual components						I/C
Patient/Caregiver Satisfaction Questionnaire						I/C
Provider Satisfaction Questionnaire						I/C
Health Resource Utilization Questionnaire						I/C
Medication-related problems						I/C

*A*, all potentially eligible patients; *B*, all eligible and interested patients; *I*, intervention patient; *C*, control patient; *I/C*, both groups

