## Strengths and limitations of this study

There is a lack of high-quality evidence on hospital discharge strategies which reduce oral anticoagulant (OAC)-related adverse events.Our methods build on our prior research showing that early post-hospital discharge is a high-risk period for adverse events for patients, that coordination of OAC management peri-hospital discharge is hypothesized to reduce events, and that virtual care may be more cost-effective than in person care.This pragmatic pilot randomized trial combines expert multidisciplinary medication management led by Clinical Pharmacology at hospital discharge with virtual care follow-up.Our feasibility outcomes introduce the concept of research resource utilization and management, expressed as cost per patient completing the trial, as a key outcome.

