### Statistical analyses

The reporting of the results of this trial will follow the CONSORT extension to pilot trials [41]. We will use descriptive statistics for presentation of baseline variables and adequacy of follow-up. Feasibility analysis including recruitment rate (≥30% is considered success), participant retention rate (≥90% to end of study is considered success), study resource utilization required (CAD $1500 per patient recruited and completing the study is considered a threshold), management assessment, and scientific assessment will be descriptive.

Analysis will use intention-to-treat methods with censoring only if the patient dies or drops out of the study with refusal of negotiated further assessments. A sensitivity analysis of the subgroup of patients who received all 3 planned follow-up intervention calls and completed the end-study data collection (per protocol analysis) will be carried out. Research staff and statisticians will review outcome data and analysis blinded to group identification.

The primary clinical endpoint will be the incidence of adjudicated AASE during the follow-up period, using proportions, and chi-square testing. Secondary endpoint analyses of the coordination and continuity of care, patient quality of life, OAC management knowledge satisfaction with care (providers & patients), and resource utilization will be analyzed using *t* tests. The incidence of the adjudicated individual clinical events (clinically relevant bleeding events, thromboembolic events, all-cause hospitalizations, and emergency department visits) will be analyzed using the methods described above for AASE. Public unit costs from Ontario will be used to cost healthcare resource utilization collected as part of the trial. Using an area under the curve approach, quality-adjusted life years (QALYs) will be determined by weighting the EQ-5D-5L health utility scores by time spent in health state. Costs and outcomes (i.e., QALYs, AASE) between the interventions will be compared from a public payer perspective. Given the short follow-up, a low risk of the trial and pilot design, no interim analysis or imputation for missing data is planned. All analyses will be performed using SAS V9.4 software (SAS Institute Inc., Cary, NC, USA).

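### The $1500 cost criterion is set per patient completing the study, but Table 1 computes cost per patient recruited, a more lenient figure whenever anyone is lost

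*Protocol article*

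**What the plan says.** All references are to the protocol article.

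- **Table 1, study resource utilization, criterion for success:** "< $1500 per patient recruited and completing the study".
- **Same row, outcome measure:** "Study costs per patient recruited".
- **Same row, method of analysis:** "Cost of personnel, supplies, travel, etc., to run the study/# patients recruited".
- **Statistical analyses:** "CAD $1500 per patient recruited and completing the study is considered a threshold".
- **Strengths and limitations of this study:** the outcome is "expressed as cost per patient completing the trial, as a key outcome". No dollar amount is given there.
- **Outcomes:** feasibility requires, among other things, that the team "spend no more than $1500 per patient running the trial". No divisor is named.

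Table 1 treats recruitment and completion as different states. Recruited means that consent was signed; completing means that the 3-month end-of-study assessment was done. The ratio of the two is the retention rate, itself a primary feasibility outcome with a target of at least 90%.

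**The concern.** Within one table row, the threshold and the formula meant to test it have different denominators. The two agree only if nobody is lost between consent and month 3, and the plan itself tolerates a loss of up to 10%.

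The Outcomes section makes feasibility depend jointly on recruitment, retention and cost, and uses the result to judge whether a definitive trial can be managed and funded. An analyst who follows the method column would report a figure that is systematically lower than the one the threshold describes. Because both versions are in print, the choice between them could also be made after the spend is known.

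**Working it through.** **Inputs**
- Threshold: $1500 (Table 1; Outcomes; Statistical analyses). It is a chosen limit with no derivation in the article, so there is nothing to reproduce.
- Retention target: at least 90% (Table 1; Outcomes; Statistical analyses).
- Sample size: 59 (Sample size estimation). This reproduces: ln(0.05)/ln(0.95) = 58.40, rounded up to 59, and 1 − 0.95^59 = 0.9515.
- Site quota: 10 to 12 at each of 6 hospitals, hence 60 to 72 patients (Recruitment methods; Trial design and setting).

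**Relation between the two figures**

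Let S be total spend, N the number recruited, C the number of completers and r = C/N.

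Cost per completer = S/C = (S/N)/r.

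The ratio of the two figures is 1/r. If the retention criterion is met (r ≥ 0.90), the ratio is at most 1/0.90 = 1.11.

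**Per-patient scale**
- r = 0.90: $1500 per recruited patient is 1500/0.90 = $1667 per completer. The completer limit expressed per recruited patient is 1500 × 0.90 = $1350. Spend from $1350 to just under $1500 per recruited patient gives opposite answers.
- r = 0.95: 1500/0.95 = $1579 per completer; the discordant range starts at 1500 × 0.95 = $1425.
- r = 1: the two figures coincide.

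**Total-spend scale**

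The completer limit is $1500 × C and the recruited limit is $1500 × N, so the gap is $1500 for each patient lost. C is the smallest number that still meets 90% retention.

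| N | C | Retention | Limit per recruited | Limit per completer | Gap |
|---|---|---|---|---|---|
| 59 | 54 | 91.5% | $88,500 | $81,000 | $7,500 |
| 60 | 54 | 90.0% | $90,000 | $81,000 | $9,000 |
| 72 | 65 | 90.3% | $108,000 | $97,500 | $10,500 |

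**Illustration (assumed spend; the article gives none)**

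With S = $85,000, N = 59 and C = 54, cost is 85,000/59 = $1441 per recruited patient, which passes, and 85,000/54 = $1574 per completer, which fails. Retention passes in both cases.

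**Boundary**

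Table 1 requires a cost strictly below $1500; the Outcomes section allows exactly $1500. A cost of exactly $1500 fails the first and passes the second.

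**The case against.** The strongest reply is that this is a slip of wording. The analysis is descriptive, no calculation in the article is wrong, both counts will be available anyway, and three places already point to completers as the intended denominator. The effect is capped at about 11% where it can alter the decision, and needs a spend within a limited range. No actual or budgeted spend is given, so nothing shows that this range will be reached.

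Most of that stands, and it limits the size of the point. It does not remove it. Table 1 defines recruited and completing separately, so the terms cannot be read as synonyms. Nor is this detail left to a fuller document: the article states two incompatible definitions rather than omitting one.

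A reader might infer more than the article supports:

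- **Start-up costs distort the average.** The Outcomes section speaks of "estimated resources required per patient to complete the main trial", and one might suppose that the formula spreads one-off set-up spending over a small pilot. The article does not say that set-up is included; its wording refers to running the study. It gives neither a set-up cost nor a size for the main trial.
- **The damage grows as retention falls.** Arithmetically it does, but below 90% retention the joint feasibility rule has already failed, so the cost divisor cannot change the overall verdict.
- **Deaths before month 3 should count as completions.** Table 1 ties completion to the 3-month assessment and makes no such exception.
- **The completer threshold is stated three times.** The dollar figure is attached to completers twice, in Table 1 and in Statistical analyses. The strengths section supports that denominator but states no threshold.

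**Conclusion.** The point holds for the denominator. As written, the Table 1 formula tests a primary feasibility threshold against a quantity other than the one the threshold names, and it is the more lenient of the two whenever retention is below 100%.

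Given that the retention criterion is met, the two figures differ by at most about 11%. With 59 recruited and 54 completers, any total from $81,000 to just under $88,500 passes by the formula and fails by the criterion. A discordant result is possible, not certain: it requires some loss to follow-up and a spend inside that range, and the actual spend is unknown.

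The conclusion assumes that a patient recruited and completing is simply a completer, which follows because every completer was first recruited. The mismatch at exactly $1500 is a smaller, separate inconsistency.

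**What to change.** 1. In Table 1, change the outcome measure and the divisor to the number of patients who complete the 3-month end-of-study assessment, which is the table's own definition of completion.
2. Name the same denominator in the Outcomes section, which now gives none, and keep it in Statistical analyses.
3. Choose either strictly below $1500 or at most $1500, and use it in every place.
4. Report cost per recruited patient alongside, as a descriptive figure that does not decide feasibility.

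This takes a few words and no new data. The price is a slightly less favourable cost figure, by up to about 11% if retention meets its target. The change should be made before the study's cost total is known, so that the choice of divisor cannot depend on the result.

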## Abstract

**Background:**

Oral anticoagulants (OACs) are commonly prescribed, have well-documented benefits for important clinical outcomes but have serious harms as well. Rates of OAC-related adverse events including thromboembolic and hemorrhagic events are especially high shortly after hospital discharge. Expert OAC management involving virtual care is a research priority given its potential to reach remote communities in a more feasible, timely, and less costly way than in-person care. Our objective is to test whether a focused, expert medication management intervention using a mix of in-person consultation and virtual care follow-up, is feasible and effective in preventing anticoagulation-related adverse events, for patients transitioning from hospital to home.

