**Methods and analysis:**

A randomized, parallel, multicenter design enrolling consenting adult patients or the caregivers of cognitively impaired patients about to be discharged from medical wards with a discharge prescription for an OAC. The interdisciplinary multimodal intervention is led by a clinical pharmacologist and includes a detailed discharge medication reconciliation and management plan focused on oral anticoagulants at hospital discharge; a circle of care handover and coordination with patient, hospital team and community providers; and early post-discharge follow-up virtual medication check-up visits at 24 h, 1 week, and 1 month. The control group will receive usual care plus encouragement to use the Thrombosis Canada website.

The primary feasibility outcomes include recruitment rate, participant retention rates, trial resources management, and the secondary clinical outcomes include adverse anticoagulant safety events composite (AASE), coordination and continuity of care, medication-related problems, quality of life, and healthcare resource utilization. Follow-up is 3 months.

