**Discussion:**

This pilot RCT tests whether there is sufficient feasibility and merit in coordinating oral anticoagulant care early post-hospital discharge to warrant a full sized RCT.

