### Sample size estimation

Pilot RCT guidance suggests that where sample size is calculated, it be based on the ability to detect a significant feasibility problem that might interfere with a subsequent full-size RCT—for example, difficulty with recruitment and retention, accuracy of outcome event capture and adjudication, frequency of events, and costing suggesting the intervention is not remotely cost-effective [55]. If a feasibility problem exists at a rate of 5% probability, it can be identified with 95% confidence with a sample of 59 participants [55].

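### The pilot is sized only to detect feasibility problems, yet clinical outcomes carry directional success criteria and significance tests that about 30 patients per arm cannot support

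*Protocol article*

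**What the plan says.** **Sizing.** Sample size estimation cites pilot guidance that, where a size is calculated, "it be based on the ability to detect a significant feasibility problem that might interfere with a subsequent full-size RCT". The figure follows: "If a feasibility problem exists at a rate of 5% probability, it can be identified with 95% confidence with a sample of 59 participants". No clinical effect size or power is given.

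**Clinical criteria and tests.** Table 1 has a column of criteria for success. Part B fills it with directional statements without a magnitude: "Intervention group will have fewer AASE compared to the control group" for AASE, and "Intervention will have lower event rates than control" for the individual events. Most of these rows name a significance test.

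**Statistical analyses.** This section calls the feasibility analysis descriptive. It then prescribes tests for the clinical endpoints, beginning with AASE: "The primary clinical endpoint will be the incidence of adjudicated AASE during the follow-up period, using proportions, and chi-square testing". It adds t tests for satisfaction and resource utilization.

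**Aims.** The Abstract (Background) asks whether the intervention "is feasible and effective in preventing anticoagulation-related adverse events, for patients transitioning from hospital to home". The Abstract (Discussion) says the pilot "tests whether there is sufficient feasibility and merit in coordinating oral anticoagulant care early post-hospital discharge to warrant a full sized RCT".

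**Progression.** Under Outcomes, feasibility is achieved with at least 30% of eligible patients recruited, 90% retained, and no more than $1500 spent per patient. No clinical result enters that rule.

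**The concern.** The design and the clinical analysis serve different purposes. The number of patients answers whether a larger trial can be run. The clinical rows of Table 1 are laid out as if the pilot could also answer whether the intervention works: each states what success looks like, and most name a test. Nothing in the article calls these comparisons exploratory, although the descriptive label is used for feasibility.

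Two misreadings of the results are at stake. A nominally significant or merely favourable clinical result could be reported as a success criterion met, and so as evidence of effectiveness or merit. A null AASE result could be read as evidence against the intervention when the sample had little chance of showing a benefit.

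**Working it through.** **1. The plan's own figure.** Chance of seeing at least one instance of a problem with probability 0.05: 1 − 0.95^n ≥ 0.95, so n ≥ ln(0.05)/ln(0.95) = 58.40, giving 59. Check: 1 − 0.95^59 = 0.9515 and 1 − 0.95^58 = 0.9490. The figure is correct for its purpose. Recruitment methods gives 10–12 patients at each of 6 sites, so 60–72 in all, or 30–36 per arm at 1:1 (the ratio is assumed).

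**2. Count of comparisons.** Table 1, part B, gives both a directional criterion and a test to AASE (chi-square), and to continuity of care, quality of life, knowledge, medication problems and four individual event types (t tests): 1 + 4 + 4 = 9. Statistical analyses adds t tests for satisfaction (patients and providers), making 11, and for resource utilization, which has no directional criterion of its own. Cost-effectiveness has a criterion but no significance test.

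**3. AASE, criterion read as a significant test.** Assumptions: 30 per arm, two-sided 0.05, uncorrected chi-square, 3-month risks not given in the article. With a and b events and t = a + b, X² = 60(a − b)²/[t(60 − t)], rejecting above 3.84. Summing the exact binomial probabilities:

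| Control risk | Intervention risk | P(p<0.05) | Per arm for 80% power |
|---|---|---|---|
| 10% | 5% | 0.106 | 435 |
| 20% | 10% | 0.194 | 199 |

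At 36 per arm the same enumeration gives 0.131 and 0.225.

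**4. AASE, criterion read literally.** With equal risks, P(fewer events in the intervention arm) = [1 − P(tie)]/2:

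| Common risk | P(tie) | P(fewer) |
|---|---|---|
| 5% | 0.246 | 0.377 |
| 10% | 0.174 | 0.413 |
| 15% | 0.145 | 0.428 |
| 20% | 0.129 | 0.436 |

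Steps 3 and 4 are alternative readings of one criterion. It is uninformative under either.

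**5. The t tests.** The difference detectable with 80% power at 29.5 per arm is (1.960 + 0.842) × √(2/29.5) = 0.73 SD.

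**6. Chance findings, for illustration only.** Nine tests, no true effect, an assumed 0.05 each:

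| Dependence | Either direction | Favouring intervention |
|---|---|---|
| Independent (1 − 0.95^9; 1 − 0.975^9) | 37% | 20% |
| Correlation 0.5 | 27% | 13% |
| Correlation 0.8 | 17% | 8% |
| Simulated trial structure, 30 per arm | 25–35% | 13–19% |

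The last row uses overlapping event outcomes (2–10% for each AASE component, 25–40% for hospital or ED visits), all tested by chi-square, and continuous outcomes correlated at 0.3.

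**7. Places that disagree.**

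| Item | One place | Another place |
|---|---|---|
| Rank of AASE | Secondary clinical (Abstract, Methods; Outcomes) | Primary clinical (Table 1; Statistical analyses) |
| Satisfaction | Descriptive (Table 1) | t test (Statistical analyses) |
| Individual events | t tests (Table 1) | Same method as AASE (Statistical analyses) |

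**The case against.** The strongest reply is that the article already ranks its aims. Objectives marks feasibility as primary and the clinical aims as secondary. Table 1 and Statistical analyses name AASE as the one primary clinical outcome, and the two labels for AASE can mostly be read together: secondary in the trial, first among the clinical outcomes. That stands. A reader might infer that there is no hierarchy at all, which the text does not support. What remains is an inconsistent label, and a ranking that is not a testing order.

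A reader might also infer that a chance clinical finding can trigger the full trial. The documents do not support this. The only numerical rule is the feasibility rule under Outcomes, and no sentence ties merit to a p-value. Sample size estimation lists event frequency and implausible cost-effectiveness among possible feasibility problems, which offers another reading of merit. The family-wise figures therefore do not measure the error of any decision rule.

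The missing alpha and multiplicity rule are not defects here, since an analysis plan that is not shown may hold them. Nor do twelve comparisons each have a criterion and a test; nine do in Table 1. Finally, the word hypothesis in part B's header row may be a heading displaced in extraction, so nothing rests on it.

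The reply does not remove the directional success criteria, the tests and the effectiveness aim from a design sized for something else. An alpha stated elsewhere would leave all three in place. The commitment to the CONSORT pilot extension for reporting does not label these comparisons either.

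**Conclusion.** The concern holds as a problem of interpretation and consistency. The 59 is right for feasibility, but it cannot carry the clinical criteria set beside it. A halving of AASE would be missed more than 80% of the time at control risks of 10% to 20%, and the criterion read literally is met in roughly two of five trials with no effect. Neither outcome would tell the reader whether the intervention works.

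These figures assume about 30 per arm, 1:1 allocation, a two-sided 0.05 level and the stated event risks, none of which the article fixes except the approximate total. At 36 per arm the conclusion is the same. The disagreements on AASE's rank and on the methods for satisfaction and individual events need no assumption. The point falls short of a flawed progression rule: that rule is feasibility-only and should stay so.

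**What to change.** - In Statistical analyses and Table 1, part B, state that all clinical and patient-reported comparisons, AASE included, are exploratory and will be reported as between-arm differences with 95% confidence intervals, without claims of effectiveness. The interval shows the limits plainly: for 10% versus 5% at 30 per arm its half-width is about 1.96 × √(0.10×0.90/30 + 0.05×0.95/30) = 13 percentage points.
- Retitle part B's success criteria as hypotheses for the main trial.
- Give AASE one rank throughout, for example secondary exploratory outcome and candidate primary for the main trial.
- Choose one method each for satisfaction and for the individual events, and use it in both places.
- State that progression rests on the feasibility criteria under Outcomes, and bring the Abstract's wording on effectiveness and merit into line.

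Cost: wording only, with no added patients or data. The pilot gives up a claim of clinical effectiveness that its size could not support.
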